### Data analysis (statistical analysis plan)

The characteristics of the patients will be summarised descriptively, using means (SD) or number (%). Feasibility outcomes will be summarised by a descriptive analysis according to number and level of data completeness (expressed as a percentage value), including reporting the number of identified PwID who have been prescribed more than 2 APTs yearly over 7 years (Objective 1), the number and proportion (%) of PwID with complete data on oral and long-acting intra-muscular injectable APTs for each of the 7 years (Objective 2), and the number and proportion (%) of identified PwID at each site with calculable chlorpromazine equivalent dose values (14, 25) at each census date for each of the 7 years of interest (Objective 3).

To explore if APT prescribing has changed between 2017 and 2023 using chlorpromazine equivalent doses (Objective 4), the equivalent dose values per PwID in receipt of multiple APTs will be calculated and summarised using mean (SD) and median (IQR), where appropriate, by site and year. A mixed effects regression model will be used to determine changes in chlorpromazine equivalent dose values across time, including year as a fixed covariate and site as random effect. A subgroup analysis will explore these trends, by including as a fixed effect, the presence of mental health indications (Objective 5). To explore the impact of the COVID-19 pandemic on multiple APT prescribing among PwID (Objective 6), a time varying COVID variable will be added to the regression model.

The SPC tool will be used to compare trends in multiple APT prescribing both within and across participating healthcare trusts and explore if the SPC tool (10) can be utilised to track yearly oral and depots antipsychotic treatment prescribing and monitor variation between services and patient groups (Objective 7).

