Before similar methodology can be used to inform future studies, it is necessary to conduct this feasibility study to ensure that the study procedures allow the objectives to be met.

The feasibility objectives of the study are to evaluate whether it is:
(1)Feasible to identify PwID who have been prescribed ≥2 APTs over 7 years retrospectively.(2)Possible to obtain a complete data set for each patient identified and therefore be able to explore the prescribing patterns across the eight sites.(3)Feasible to quantify APT prescribing in PwID as Chlorpromazine equivalent dose values across different Healthcare Trusts in England and Wales.The main objectives of the study are to investigate:
(4)Yearly and overall prescribing patterns among PwID [with or without mental health reasons (co-occurring mental health conditions)] in receipt of ≥2 forms of APT over time.(5)How multiple APT prescribing has changed between 2017 and 2023 using chlorpromazine equivalent dose values, in PwID with mental health and no mental health indications.(6)The impact of the COVID-19 pandemic (and corresponding lockdown restrictions in England and Wales) on multiple APT prescribing among PwID.(7)Whether the SPC tool be utilised to track yearly APT prescribing among PwID receiving multiple forms of APT, and monitor variation between services (sites) and patient groups (e.g., psychiatric co-morbidities; challenging behaviour).

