## Methods and analysis

### Study design

This is a multi-site cross-sectional study, involving data collection from specialist adult ID services based within eight NHS healthcare trusts across England and Wales over a seven-year time span (2017–2023). The eight trusts serve areas comprising of differing levels of urbanisation and pandemic-related lockdown restrictions to allow for the comparison of the impact of the COVID-19 pandemic on multiple APT prescribing among PwID.

The participating trusts are listed below, alongside their overall estimated catchment area:
•North East London NHS Foundation Trust (4.3 million) (16).•Cheshire and Wirral Partnership NHS Foundation Trust (1 million) (17).•Central and North West London NHS Foundation Trust (3 million) (18).•Cornwall Partnership NHS Foundation Trust (450,000) (19).•Coventry and Warwickshire Partnership NHS Trust (1 million) (20).•Hertfordshire Partnership University NHS Foundation Trust (400,000) (21).•Leicestershire Partnership NHS Trust (1.1 million) (22).•Swansea Bay University Health Board (390,000) (23).

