### Patient eligibility criteria and identification

#### Inclusion criteria

Patients must satisfy all the following criteria to be enrolled in the study:
(1)Having received a psychiatric review by specialist adult ID services within the last year^1^(2)A diagnosis of ID(3)Being under the care of specialist adult ID services within the last year of the date of interest(4)In receipt of ≥2 APTs [oral and/or IM injectable (depots)]^1^For a patient to be included on 1st June 2017, data is to be extracted from the most recent psychiatric review within the period between 1st January 2017–31st December 2017.

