#### Exclusion criteria

Patients who meet any of the following criteria will be excluded from study participation:
(1)Under the age of 18 years(2)Patients treated with ClozapinePatients treated with Clozapine are excluded from the study as the drug is primarily used to treat specifically treatment-resistant Schizophrenia, whereby patients have been insufficiently responsive and/or intolerant of other APTs (24). Therefore, there would be a high likelihood that a patient treated with Clozapine has an appropriate diagnosis. Furthermore, those prescribed Clozapine are more likely to receive a more enhanced service due to the drug's side effect profile and the requirement for frequent blood monitoring (24), which is likely to differ from most PwID who are prescribed other antipsychotics, who encountered a lack of physical health reviews during the COVID-19 pandemic (9).

This is a retrospective multi-centre cohort study whereby patients are de-identified at site and thus patient consent is not required. At each site, the direct clinical care team (consultant, trainee doctor or specialist nurse) or a research nurse will identify 7–10 adult ID patients on their caseloads for each of the census dates. The patients who were prescribed ≥2 APTs will be identified from the paper-based clinic letters, inhouse databases (e.g., clinical portal bespoke)/electronic systems (e.g., SystmOne, Rio, Care Notes). Data will be extracted from the patient's most recent clinic letter to the census date (1st July of specified year), either up to 6 months before or 6 months, i.e., for July 2017, between 1st January 2017 and 31st December 2017. See Figure 1 for the study flow chart.

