### Outcome measures

Data for patients will be collected using standardised data entry forms, for each of seven consecutive years (2017–2023). Data collected (Table 1) will include basic demographic details (age, gender, ethnicity, residential circumstances), clinical data (ID classification, genetic variants, medical co-morbidities, epilepsy, neurodevelopmental conditions, neurodegenerative conditions, psychiatric co-morbidities, challenging behaviour), and data on the APT (first/second generation, dose, units, frequency, route of administration, reason for prescribing).

**Table 1 T1:** Data collection at each yearly time point (1st July 2017–2023).

			Timepoints yearly 01/07/2017–01/07/2023^a^
Caseload number on 2 or more antipsychotic treatments identified			
Date of nearest clinic letter			x
Demographics			
Age	Date of birth (month/year)		x
Gender	Male		x
	Female		x
	Gender non-conforming		
Ethnicity	Asian, Asian British, Asian Welsh		x
	Black, Black British, Black Welsh, Caribbean or African		x
	Mixed or multiple ethnic groups		x
	White		x
	Other ethnic group		x
Place of residence	Family home		x
	Residential home		x
	Supported living		x
	Living independently		x
	Other (describe)		x
ID classification			
ID classification	Mild		x
	Moderate/Severe/Profound		x
Genetic variants	Fragile X syndrome		x
	Down syndrome		x
	Tuberous sclerosis complex		x
	Developmental and/or epileptic encephalopathy		x
	Other		x
Clinical characteristics			
Co-occurring medical conditions^b^	Obesity		x
	Constipation (regular laxatives)		x
	Cerebral palsy and other paralytic syndromes		x
	Osteoporosis		x
	Epilepsy		x
	Metabolic syndromes	Diabetes	x
		Hypertension	x
		Dyslipidaemia	x
		Cardiovascular disease	x
	Other		x
Neurodevelopmental conditions	Autism spectrum disorder (ASD)		x
	Attention deficit hyperactivity disorder (ADHD)		x
Neurodegenerative conditions	Dementia		x
Co-occurring psychiatric conditions	Psychosis (Schizophrenia/schizoaffective disorder, bipolar affective disorder, severe depression with psychotic conditions or other		x
	Depressive disorders		x
	Anxiety disorders (obsessive compulsive disorder (OCD), Post-traumatic stress disorder (PTSD) or other		x
Challenging behaviour	Yes/no/not recorded		x
Antipsychotic drugs			

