### Target sample size and justification

As this is a feasibility study no formal power calculation has been performed. The aim is for each site to collect between 7 and 10 patient's data per annum. Hence, the estimated study size will be approximately 392–600 patients for the seven-year period. It is estimated that there will be a high number of PwID receiving multiple oral and depot APTs each year which was estimated after discussion with the eight sites of their caseloads and the numbers expected on at least two oral and depots APTs and the duration they have been on review lists.

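### The Objective 1 feasibility outcome is worded as a count of people on more than two antipsychotics, whereas the objective, the eligibility rule and the data collection all use two or more

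*Protocol article*

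**What the plan says.** The section Data analysis (statistical analysis plan) links each feasibility objective to a reported quantity. For the first it specifies "reporting the number of identified PwID who have been prescribed more than 2 APTs yearly over 7 years (Objective 1".

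Elsewhere the article sets the threshold at two or more:

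- Objective 1, in the Introduction: "Feasible to identify PwID who have been prescribed ≥2 APTs over 7 years retrospectively".
- Inclusion criterion 4: "In receipt of ≥2 APTs [oral and/or IM injectable (depots".
- The identification procedure, under Exclusion criteria: "The patients who were prescribed ≥2 APTs will be identified from the paper-based clinic letters".
- Table 1, under Outcome measures: "Caseload number on 2 or more antipsychotic treatments identified".
- Target sample size and justification, where the sites' estimates concerned "the numbers expected on at least two oral and depots APTs".

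**The concern.** More than two drugs means three or more. The analysis sentence cites Objective 1 by number and then counts a narrower group than that objective names. A person on exactly two antipsychotics satisfies the objective and the inclusion criterion and has a record, but is outside the outcome as worded.

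The instruction could be carried out without anyone noticing a problem. Table 1 records each drug with its dose, so an analyst could select the records with three or more drugs and report that number. The result would answer a question that the study did not ask. The article says that the study is meant to inform the design of a wider registry, and whether eligible people can be found is part of what it sets out to learn.

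**Working it through.** No power formula or published figure applies to this point, so the check is mainly a comparison of wording.

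**Step 1. Set the thresholds side by side.**

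| Place in the protocol article | Threshold | Exactly two drugs included? |
|---|---|---|
| Introduction, Objective 1 | ≥2 | yes |
| Inclusion criteria, item 4 | ≥2 | yes |
| Exclusion criteria, identification procedure | ≥2 | yes |
| Outcome measures, Table 1, caseload row | 2 or more | yes |
| Target sample size and justification | at least two | yes |
| Data analysis, outcome for Objective 1 | more than 2 | **no** |

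Five places agree and one differs. The one that differs is the one that defines the reported outcome.

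**Step 2. Look for a reason for a stricter threshold.** None is given. No section describes a subgroup on three or more drugs, and no other objective refers to one.

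**Step 3. Ask which count the collected data support.** The caseload item in Table 1 is already defined at two or more. No caseload count above two is listed. The literal outcome could be derived only from the drug entries of the individual records, of which each site aims to collect 7 to 10 a year.

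**Step 4. Ask what else depends on the phrase.** Eligibility is fixed by criterion 4, so enrolment does not change. The dose summaries and models refer to people on multiple antipsychotics and do not repeat the stricter wording. The outcomes for Objectives 2 and 3 have their own numbers and proportions.

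**Step 5. Ask how large the loss would be.** Let N be the number of records and s the share on exactly two drugs. The correct count is N and the literal count is N × (1 − s). The article does not give s.

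For N, the design is "based within eight NHS healthcare trusts across England and Wales over a seven-year time span (2017–2023", which is 8 sites and 7 years. At 7 to 10 records per site and year:

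- lower end: 8 × 7 × 7 = 392
- upper end: 8 × 7 × 10 = 560

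The article states 392–600. The lower end reproduces and the upper end does not, but that is a separate matter and does not bear on this point.

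As illustration only, with assumed values of s:

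| Assumed share on exactly two | Literal count out of 392 | Literal count out of 560 |
|---|---|---|
| 50% | 392 × 0.50 = 196 | 560 × 0.50 = 280 |
| 80% | 392 × 0.20 = 78 | 560 × 0.20 = 112 |
| 95% | 392 × 0.05 = 20 | 560 × 0.05 = 28 |

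The spread, from 20 to 280, shows how little can be said without s. N is also a collection target and not an estimate of how many eligible people the services have.

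**The case against.** The strongest reply is that nobody would apply the phrase literally. The sentence counts identified people, identification is by two or more drugs, and the caseload item is recorded at two or more. An analyst who reads the whole article would probably use two or more. Because the individual drugs are recorded, the right count could also be recovered later.

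Most of this stands. It makes a verbal slip much more likely than a deliberate choice, and it limits the harm. It does not make the sentence correct. Among people identified by two or more drugs, a count of those on more than two is a coherent instruction, so the text permits two different answers.

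A reader might be tempted to go further in four ways, none of which the document supports:

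- *The counted group would be much smaller than the enrolled one.* This needs the share on exactly two drugs, which is not given.
- *The percentages for Objectives 2 and 3 would be wrong.* Objective 1 is a plain number, and neither of the other outcomes names it as its denominator.
- *The headline result, or the size of the registry, is at stake.* This is one of three feasibility objectives, and the article says only that the study as a whole informs the registry's design.
- *The study meant to focus on people on three or more drugs.* Nothing in the article says so.

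**Conclusion.** The inconsistency is real and the outcome for Objective 1 is wrong as written. It states a threshold of three or more where the objective, eligibility, identification, data collection and sample size rationale use two or more. If the wording is followed, eligible people on exactly two antipsychotics drop out of the first feasibility count.

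This conclusion rests on the text alone and needs no assumption about the split. The number lost cannot be computed from the document, and the illustrative figures depend entirely on assumed shares. The error is confined to this one reported count.

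**What to change.** In Data analysis (statistical analysis plan), replace the threshold in the Objective 1 outcome with *2 or more (≥2) APTs*. Confirm that the analysis code, and any fuller analysis plan, apply ≥2 for this count.

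The change touches no data collection, eligibility rule or other analysis, and costs nothing. Reporting how many people were on exactly two and how many on three or more would be a useful descriptive line, but it is optional and not part of the correction.

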## Discussion

There is a clear rationale for developing a database that establishes the antipsychotic prescribing patterns across specialist adult ID services, so that trends and patterns can be identified and further evaluated to improve the healthcare of PwID. Previous data has reported on prevalence prescribing rates, rather converting the APTs into dose equivalent values which can be input into the SPC tool to evaluate and measure ID specialist use of APTs in PwID across the UK. Furthermore, previous research has tended to report on entire clinical populations of PwID, rather than specifically a focus on those in receipt ≥2 different forms of APTs. This, along with the fact that there is currently no clinical rationale or evidence to support ≥2 different APTs being prescribed, supports the idea that there a need for a database to address this issue. However, the development of a de-identified database can present a series of unique benefits and challenges.

The limitations of the study are inherent to the use of routine health data. The use of routinely collected data means that the data quality and data completeness between sites might be vastly different. Site teams are encouraged to extract data from multiple sources, including clinic letters, inhouse databases and electronic or paper note systems. However, some of the data being collected might not be evident in any of these places and could potentially be difficult to find. This was acknowledged as a potential difficulty during study development and one of the feasibility objectives of the study is to evaluate whether it is indeed feasible to obtain a complete (or near complete) data set for each patient. An additional limitation of the study is that some patients may be in receipt of one or more of their APTs on a short-term basis.

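### Objective 2 asks for a complete data set per patient, but the measure assigned to it counts completeness of antipsychotic data only

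*Protocol article*

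**What the plan says.** Among the feasibility objectives in the Introduction, Objective 2 asks whether it is "Possible to obtain a complete data set for each patient identified and therefore be able to explore the prescribing patterns across the eight sites". The Discussion restates the aim as obtaining "a complete (or near complete) data set for each patient", just after acknowledging that some of the items sought may not be found in any source.

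The Outcome measures section says what the data set contains. It lists "basic demographic details (age, gender, ethnicity, residential circumstances", then "clinical data (ID classification, genetic variants, medical co-morbidities, epilepsy, neurodevelopmental conditions, neurodegenerative conditions, psychiatric co-morbidities, challenging behaviour", and then data on each antipsychotic: generation, dose, units, frequency, route and reason for prescribing. Table 1 sets these out in more detail.

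The Data analysis section opens with a general statement: "Feasibility outcomes will be summarised by a descriptive analysis according to number and level of data completeness (expressed as a percentage value), including reporting". It then gives one measure per feasibility objective. The one labelled for Objective 2 is the number and proportion of people "with complete data on oral and long-acting intra-muscular injectable APTs for each of the 7 years (Objective 2". Objective 3 is measured by the number and proportion with calculable chlorpromazine equivalents.

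**The concern.** The objective and its measure cover different things. The objective concerns the whole record; the measure concerns the antipsychotic part of it. A record with every drug detail present but no ID classification, no psychiatric co-morbidity status and no ethnicity would count as a success under the measure and a failure under the objective.

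This matters because later objectives use the uncounted fields. Objective 7 looks at variation between patient groups and gives psychiatric co-morbidities and challenging behaviour as its examples. Objective 5 splits by mental health indication, which may be taken from the psychiatric-condition fields. The Introduction also names gender, ethnicity, residence, level of ID and co-occurring conditions as factors the work should help to explain. The study is meant to inform the design of a wider registry, and for that the designers need to know which of these fields can be retrieved from routine records. An antipsychotic-only percentage does not tell them.

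**Working it through.** The plan states no completeness figure, so there is nothing to reproduce. The check is one of definitions, followed by an illustration on assumed rates.

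**Step 1: count the items** (Outcome measures, running text).
- Demographic: age, gender, ethnicity, residential circumstances = 4.
- Clinical: the eight items from ID classification to challenging behaviour = 8.
- Antipsychotic: generation, dose, units, frequency, route, reason = 6.
- Total 4 + 8 + 6 = 18. The Objective 2 measure covers the last 6; the other 12 are outside it.

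**Step 2: direction.** With the same denominator, every record with a full data set also has complete antipsychotic data. Hence P(full) ≤ P(antipsychotic complete). The two are equal only if no record with complete antipsychotic data lacks any of the other 12 items. This needs no assumption about rates.

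**Step 3: illustration.** Let a be antipsychotic completeness, q the completeness of each other item, and k = 12. If items are independent, P(full) = a × q^12. The values of a and q are assumptions; the documents give none.

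| a | q | P(full) | Gap, a − P(full) |
|---|---|---|---|
| 95% | 99% | 0.95 × 0.99^12 = 84% | 11 points |
| 95% | 95% | 0.95 × 0.95^12 = 51% | 44 points |
| 95% | 90% | 0.95 × 0.90^12 = 27% | 68 points |
| 90% | 99% | 0.90 × 0.99^12 = 80% | 10 points |
| 90% | 95% | 0.90 × 0.95^12 = 49% | 41 points |
| 90% | 90% | 0.90 × 0.90^12 = 25% | 65 points |

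On 392 records, the lower end of the stated study size, a = 95% gives about 372 records complete on the antipsychotic measure. On the full data set the count is about 330, 201 or 105 for q = 99%, 95% or 90%.

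**Step 4: drop independence.** Missing items tend to cluster within a record, which narrows the gap. For a = 95% and q = 99%, the bounds are a − 12 × (1 − q) = 0.95 − 0.12 = 83% and min(a, q) = 95%. So the gap could be anything from 0 to 12 points at those rates. Only the direction is fixed.

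**The case against.** The strongest reply is that the lead-in to the feasibility measures is general and its list is open, and that the abstract says without restriction that completeness will be evaluated. Item-level tables may well sit in the full protocol or a separate analysis plan. This stands as far as it goes: wider reporting is not ruled out. But the only measure the article ties to Objective 2 is the antipsychotic one, and no full-record measure is tied to it anywhere.

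A second reply is that Objective 2 serves the exploration of prescribing patterns, so antipsychotic completeness is a sensible headline. It is a relevant component. Yet the patterns are to be compared between patient groups, and those groups are formed from the uncounted fields.

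Several stronger readings are tempting, and the documents do not support them:
- *The antipsychotic data are complete by construction, because entry requires two or more drugs.* Eligibility needs only receipt of the drugs. A letter can name both and omit a dose, a frequency or a reason, so the measure can fail.
- *Reason for prescribing is left out.* The Outcome measures section places it within the antipsychotic data. That also softens the consequence for Objective 5, whose indication could be read from that field.
- *Unrecorded items will be read as absent.* Table 1 shows "Yes/no/not recorded" for challenging behaviour, and reason for prescribing has its own code for an unclear indication. How the other items are coded depends on data entry forms that are not shown.
- *The measure merely duplicates Objective 3.* They overlap, but a fully recorded drug entered as free text may have no conversion factor.
- *A go/no-go decision hangs on the figure.* No such rule is stated; the study is to inform registry design.

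**Conclusion.** The mismatch is real and lies in the article's own text. The measure labelled Objective 2 does not answer Objective 2 as the Introduction and Discussion set it. It cannot understate full-record completeness, and it overstates it whenever a record with complete antipsychotic data lacks a demographic or clinical item. The Discussion's warning that some items may not be found makes that a realistic prospect, although it names no fields.

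The size of the overstatement cannot be derived from the documents. The range of about 10 to 68 points holds only for the assumed rates, 12 items and independence, and should not be quoted as an estimate. It does show that small losses per item can add up across 12 items. The point deserves correction because it affects one of three feasibility objectives. It does not make the study unsound, and antipsychotic completeness remains worth reporting.

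**What to change.** In the Data analysis section, define the Objective 2 measure as the number and proportion of records with all Table 1 items recorded, by site and year. If requiring every item is thought too strict, name a core set in advance that includes at least ID level, psychiatric conditions and challenging behaviour. Report item-level completeness and the present antipsychotic-only proportion beside it, so that readers can see where records fail.

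An entry that the indication is not clear need not count as incomplete: in a study of prescribing practice it may be a finding in itself. The plan should simply say how it is treated.

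The cost is a change of wording and one table from data already entered, provided the database separates unrecorded from absent. The downside is that the headline completeness figure can only stay the same or fall.

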First generation APTs (most common brand name)^c^	Chlorpromazine (Largactil)—Levomepromazine (Nozinan)—Pericyazine (Neulactil)—Prochlorperazine (Stemetil)—Promazine—Trifluoperazine (Stelazine)—Benperidol (Frenactyl)—Haloperidol (Haldol)—Flupenthixol (Depixol; Fluanxol)—Zuclopenthixol (Clopixol)—Pimozide (ORAP)—Sulpiride		x
Second generation APTs (most common brand name)^c^	Amisulpride (Solian—oral route)—Aripiprazole (Abilify)—Asenapine—Cariprazine—Lurasidone—Olanzapine—Paliperidone—Quetiapine—Risperidone		x
Other^c^	Pipothiazine—Penfluoridol—Fluphenazine—Thioridazine—Other (free text)		x
Reason for each APT prescribed	Psychotic disorder		x
	To manage specific behavioural challenges/agitation		x
	To augment other psychotropic medication		x
	Anxiety disorder		x
	Other		x
	Not clearly indicated		x

^a^
Time-point: Most recent clinic letter to the 1st of July of the year under study; 6 months either side (e.g., 01/06/2017: between 1st January 2017 and 31st December 2017).

^b^
Co-occurring medical conditions, based on those most commonly reported in patients with ID.

^c^
Dose, units, frequency, and route of administration are recorded for each APT prescribed.

Data will be extracted from multiple sources for each patient by the clinical team. Source data will come from paper-based clinic letters, inhouse databases (e.g., clinical portal bespoke)/electronic systems (e.g., SystmOne, Rio, Care Notes). The yearly census date is the 1st of July and the patient's most recent information, and clinic letter will be identified (up to 6 months before or 6 months after the census date). Collected data will be anonymised at site by the clinical team and/or research nurses.

Data will be entered directly onto a study specific instance of REDCap (Research Electronic Data Capture), a secure web-based database. De-identified data will also be transferred on the SPC tool to evaluate and track the prescription changes over time. Only anonymised (de-identified) data will be available to the University of Plymouth research team/data processors for analysis. As the data is de-identified at site before being entered into the database, each year will be treated as independent even if patients are eligible year on year. There will be no patient linkage across time.

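### No planned percentage shows how often eligible people's antipsychotic data could not be located or were passed over: Objectives 2 and 3 are scored among people already identified, and Objective 1 is a bare count

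*Protocol article*

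**What the plan says.** The Introduction lists three feasibility objectives: identifying people on two or more antipsychotics (Objective 1), completeness of their data (Objective 2) and conversion to chlorpromazine equivalents (Objective 3). Objective 2 is worded "Possible to obtain a complete data set for each patient identified".

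The section Data analysis (statistical analysis plan) turns these into measures:

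- Objective 1 is a number with no denominator.
- Objective 2 is "the number and proportion (%) of PwID with complete data on oral and long-acting intra-muscular injectable APTs for each of the 7 years". This sentence names no denominator; the restriction to identified patients comes from the Introduction.
- Objective 3 is "the number and proportion (%) of identified PwID at each site with calculable chlorpromazine equivalent dose values". Here the denominator is explicit.

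On how people get in, the text under Exclusion criteria says: "The patients who were prescribed ≥2 APTs will be identified from the paper-based clinic letters, inhouse databases", and adds electronic systems. The Outcome measures section draws the data from the same kinds of source: "Source data will come from paper-based clinic letters, inhouse databases", again with electronic systems. Inclusion criterion 1 is "Having received a psychiatric review by specialist adult ID services within the last year". The clinical team or a research nurse identifies 7–10 patients per census date. The article gives no rule for choosing among candidates when there are more than that. Table 1 has a row for the caseload number on two or more antipsychotics identified, but the analysis section does not use it.

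**The concern.** Two different things can go wrong when routine records are used. An identified person's record may lack an item, such as dose or frequency. Or an eligible person may not reach the data set at all, because no source shows the drug list or because someone else was chosen to fill the target. The stated measures see only the first.

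Objective 1 ought to cover the second, but a count cannot do so without a denominator. Where a service has enough patients, the count will sit near 7–10 per year however many people were missed. The Identification section of the Results itself speaks of patients contributing to a site's identification target.

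This matters because the Abstract and the Discussion say the study is meant to inform the design of a wider registry. A registry needs to know what share of eligible people will yield a usable dose value. The plan supplies the share among those who have already come through.

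**Working it through.** **The plan's own figure.** The only number bearing on these denominators is the study size under Target sample size and justification, 392–600. Sites × patients per site-year × years gives:

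- lower end: 8 × 7 × 7 = 392, which agrees;
- upper end: 8 × 10 × 7 = 560, not 600;
- the Abstract's seven services: 7 × 10 × 7 = 490, its stated maximum.

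The 560 against 600 mismatch is a separate matter. What counts here is that the expected total is the product of sites, target and years. It is a quota, not an estimate of how many eligible people can be found.

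**Who enters which measure.**

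| Situation | In the denominator of Objectives 2 and 3? | Counted as failure? |
|---|---|---|
| Identified and entered, drug data complete | Yes | No |
| Identified and entered, dose or frequency missing | Yes | Yes |
| Eligible, but no source searched shows two antipsychotics | No | No |
| Eligible candidate passed over, target filled by others | Not if only entered records are scored | No |
| No psychiatric review in the year | No (ineligible) | Rightly not |

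Rows 3 and 4 are the gap. Row 4 does no harm if the choice is unrelated to the state of the record. It distorts the percentages only if poorer records are passed over more often.

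**What the gap can do.** Define:

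- *s* = share of the eligible people a site attempts who are identified and entered;
- *c* = share of those entered with complete data or a calculable dose.

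The planned percentage is *c*. The end-to-end yield is *s* × *c*, so the difference is *c* − *sc* = *c*(1 − *s*). The article gives neither rate, so the values below are assumptions and show the range only.

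| *c* | *s* = 100% | 90% | 80% | 70% | 50% |
|---|---|---|---|---|---|
| 70% | 70% | 63% | 56% | 49% | 35% |
| 80% | 80% | 72% | 64% | 56% | 40% |
| 90% | 90% | 81% | 72% | 63% | 45% |

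In counts, suppose 560 people are entered with *c* = 90% and *s* = 80%. Then 0.9 × 560 = 504 are calculable, and 560 / 0.8 = 700 eligible people were attempted. The planned report is 504/560 = 90%; the end-to-end yield is 504/700 = 72%, a difference of 0.9 × 0.2 = 18 points. The two agree only when *s* = 100%. Nothing the plan reports allows *s* to be estimated.

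**The case against.** The strongest reply is that the measures match the objectives. Identification has its own objective, Objective 2 is openly conditional on it, and completeness among identified patients is a legitimate feasibility measure. That stands. The percentages are not wrong as conditional quantities. The weakness is that Objective 1, which should supply the other factor, has no denominator.

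A reader might go further in four ways that the article does not support.

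- *That all retrieval failures escape the denominator.* They do not. A missing dose or frequency in an identified patient stays in and counts against the site.
- *That the Discussion admits the problem.* Its remark that "some of the data being collected might not be evident in any of these places and could potentially be difficult to find" concerns items within the records of included patients, which Objectives 2 and 3 do capture.
- *That a missing letter always means the person is never identified.* Several sources are searched. Someone can be found in a database or electronic system and then be scored incomplete. Someone with no review in the year is ineligible, not a retrieval failure.
- *That feasibility is overstated by a known amount, or that a site with poor records will report close to 100%.* The first needs rates the article does not give. The second needs sites to choose on completeness, which no section describes. The article gives no selection rule that would prevent it, but that is not evidence that it happens.

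It may also be said that a condensed article leaves screening logs to the full protocol, and that Table 1 already collects a caseload number. The first is fair as regards logs, but the article itself fixes the Objective 3 denominator and the Objective 1 count. The second helps only in part: the caseload row counts people identified, so it shows how far the target restricts entry but not who was missed.

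**Conclusion.** The point holds in a limited form. Objectives 2 and 3 are scored among identified people, explicitly for Objective 3 and by definition for Objective 2. Objective 1 is a count governed largely by the 7–10 target. No planned percentage therefore reflects failure to locate eligible people's antipsychotic data, or records passed over.

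The direction is certain if the percentages are read as the yield of the whole process: the conditional figure cannot be lower than the end-to-end figure. The size is unknown. At an assumed 90% among those entered, the gap runs from 0 to 45 points as *s* falls from 100% to 50%, and the article does not say where in that range the study lies. No stated progression threshold depends on these percentages, and the outcomes are descriptive. The consequence is a limit on what the study can tell the registry, not an invalid analysis.

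**What to change.** In the text on patient identification (under Exclusion criteria):

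- Where a site has more candidates than the target for a census date, take them in a random or consecutive order fixed before anyone checks completeness.
- Keep a short log per site-year of everyone attempted, with the reason for any non-entry. Separate the ineligible (no review in the year, not on two or more antipsychotics, clozapine) from those whose letter or drug list was not found.

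In Data analysis (statistical analysis plan):

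- Report Objective 1 as numbers identified and entered, beside the Table 1 caseload number.
- Report Objectives 2 and 3 twice: complete or calculable over entered, labelled as conditional on identification; and complete or calculable over attempted, leaving out confirmed ineligibles.

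Some people whose drug list was not found may not have been on two antipsychotics. The second percentage may therefore be too low, and the pair is best read as a bracket for the people attempted.

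The cost is a brief log per site-year, possibly fewer usable records, and less favourable percentages. People invisible in every source still cannot be counted, and this should be stated as a limitation. Trial status gives 01.04.2024 as the end of data collection. If no log was kept, the attempted denominator may not be recoverable; the conditional labelling and the caseload number (if recorded) can still be reported, and the log can be built into the registry design.
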